## Abstract

**Background:**

Spontaneous pregnancy loss and implantation failure after assisted reproductive technologies (ART) are very common occurrences. Although 50–60% of all cases remains unexplained, various predisposing factors, including thrombophilias, have been identified. Thus, the potential benefit of a prophylaxis with low-molecular-weight heparins in improving outcomes has been often investigated over the years. However, the majority of studies are observational and results from randomized clinical trials (RCTs) are inconclusive, probably due to heterogeneity and limited sample size. To cover these unmet needs and to have further data mainly based on the real-life clinical management, we designed these multicenter registries.

**Methods:**

OTTILIA (Observational sTudy on antiThrombotic prevention in thrombophILIA and pregnancy loss) and FIRST (recurrent Failures in assIsted Reproductive Techniques) registries are two prospective, multicenter, observational studies to evaluate pregnancy or ART outcomes in consecutive women with previous reproductive failures after spontaneous or assisted conception, respectively. All enrolled women are observed from their first visit after positive pregnancy test (OTTILIA) or before commencing a new ART cycle (FIRST) until the end of pregnancy or ART procedure (negative pregnancy test/end of pregnancy, if successful cycle), respectively. Data are collected by means of questionnaires and recorded in a central database. Follow-up investigations are performed during hospital stay, routine clinical follow-up visits or telephone interviews. Primary outcome is live birth rate in the OTTILIA register and clinical pregnancy rate in the FIRST.

**Discussion:**

Although RCTs are the ‘gold standard’ for evaluating treatment outcomes, we believe that our registries represent a valid alternative in improving knowledge on mechanisms involved in reproductive failures and supporting future clinical decisions.

**Trial registration:**

NCT 02385461, retrospectively registered 5 March 2015 (OTTILIA); NCT 02685800, registered 10 February 2016 (FIRST).

## Background

Spontaneous pregnancy loss (PL) and implantation failure after assisted reproductive technologies (ART) represent very common occurrences in women’s reproductive life.

It has been estimated that PL (generally defined as a spontaneous loss of pregnancy from conception to 20 weeks of gestation) affects up to 1000–1500/10000 pregnancies/year (10–15% of pregnancies) and about 1% of all cases is a recurrent PL (RPL) [1]. It is also known that the risk of PL increases with increasing numbers of pregnancies, regardless of previous obstetric outcomes [2]. The risk is expected to be particularly relevant when all previous pregnancies resulted in PL: the likelihood of carrying subsequent pregnancies to term is about 80% after 2 PL, compared with 55–75% after 3 PL [2].

Poor outcomes have been reported in the field of ART as well. Based on the last report by the European Society of Human Reproduction and Embryology (ESHRE), in Europe, during 2012, the mean pregnancy rate per embryo transfer was 33.8% after in vitro fertilization (IVF), 32.3% after intracytoplasmic sperm injection (ICSI), 23.1% after frozen embryo replacement and 48.8% after egg donation [3].

Although various predisposing factors have been identified in both conditions, 50–60% of all cases remain unexplained. A potential causative role of inherited (the Factor V Leiden or the prothrombin A20210 gene variants, protein C, protein S or antithrombin deficiency) or acquired (antiphospholipid-antibody syndrome) thrombophilias has been documented [4–6], presumably due to the obstruction in placental vessels caused by haemostatic disorders. Thus, the potential benefit of a prophylaxis with low-molecular-weight heparins (LMWHs) in improving the live birth rate or outcomes in ART procedures has been often investigated and demonstrated by several studies, that are mostly limited by their observational nature or the limited sample size [7–12]. On the contrary, randomized clinical trials (RCTs) on this issue have shown inconclusive results, probably due to heterogeneity and, sometimes, small number of women included [13–18]. Therefore, despite increasing knowledge on reproductive failures over the past decades, there are still several aspects of clinical management, treatment and prognosis with uncertainties that need to be addressed. As far as ART, the need for further well-designed RCTs with larger sample size has also been raised by the last Cochrane review [19]. Unfortunately, RCTs in pregnant/infertile women are often stopped before completing, due to poor and slow recruitment.

To cover these unmet needs and to have further data mainly based on the real-life clinical management, we are currently conducting the OTTILIA (Observational sTudy on antiThrombotic prevention in thrombophILIA and pregnancy loss – NCT 02385461) and FIRST (recurrent Failures in assIsted Reproductive Techniques – NCT 02685800) registries, respectively.

We summarize here the design of these studies and discuss the importance of their results in the clinical practice.

## Methods

### Aims

Primary aims of the OTTILIA and FIRST registries are: (1) to identify and evaluate all possible factors associated with reproductive outcome and improve risk stratification of women, (2) to assess the best clinical management strategies (including a potential benefit of prophylaxis with LMWH) in improving outcome, (3) to evaluate characteristics of women who possibly benefit from an antithrombotic treatment.

Secondary aims are: (1) to evaluate occurrence of ovarian hyperstimulation syndrome (OHSS) in women undergoing ovarian stimulation, obstetric and thromboembolic complications according to characteristics of women and possible treatment, (2) to evaluate, among women prescribed with pharmacological treatments, the risk of side effects.

Additional aims include evaluation of incidence, prevalence, and recurrence of reproductive failures in the ‘real word’ of women trying to get pregnant and/or to carry a pregnancy to term.

### Design and setting of the study

OTTILIA and FIRST registries are two prospective, studies designed to investigate pregnancy or ART outcomes according to different clinical and laboratory features and clinical management in women consecutively observed because of previous reproductive failures after spontaneous or assisted conception, respectively.

The possible assignment of women to treatments (such as LMWH) is not decided in advance but instead falls within current practice.

Obstetrics and Gynecology Departments as well as Thrombosis Centers with local Ethical Committee approval are allowed to participate to these studies.

Authors adhered to SPIRIT guidelines.

### Participants

All consecutive women who meet the inclusion criteria for the OTTILIA or FIRST registries (Table 1) are recruited by participating Centers on admission after obtaining informed consent. Women eligible for the OTTILIA register can undergo thrombophilia test before conception, according to local policy. If the test is not available or the test was not prescribed by the physician, women included are considered as non- carriers. As far as FIRST, knowledge of thrombophilia status is not a prerogative of the register. However, when information is available, it will be considered in final analysis.

**Table 1 Tab1:** Inclusion and exclusion criteria of the OTTILIA and FIRST registries

OTTILIA	FIRST
Inclusion criteria	
• Pregnancy confirmed by urine/blood pregnancy test or ultrasound examination • Previous recurrent otherwise unexplained PL * ≥3 or 2 PL in the presence of at least 1 normal fetal karyotype* or • At least 1 previous IUFD * A loss after 20 weeks of a morphologically normal fetus*	• ART cycle at enrolment *First, second and third level ART cycles* • 2 or more implantation failures/losses of clinical pregnancies after ART (independently of the number of embryos transferred) *At least 2 previous cycles with negative pregnancy test and/or PL after a positive pregnancy test*
Exclusion criteria	
• Personal history of venous and/or arterial thromboembolism • Allergy to LMWHs • Uterine abnormalities • Cervical incompetence • Chromosomal abnormalities in parents • Known hemorrhagic diathesis	• Uterine abnormalities • Hydrosalpinx • Chromosomal abnormalities in parents • Known hemorrhagic diathesis • Previous inclusion in the study

*PL* pregnancy loss, *IUFD* intrauterine fetal death, *ART* assisted reproductive technologies, *LMWHs* low-molecular-weight heparins

Enrolled women are free to withdraw their informed consent and exit from the study.

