### Study procedure

All enrolled women are observed from their first visit after positive pregnancy test (OTTILIA) or before commencing a new ART cycle (FIRST) until the end of pregnancy or ART procedure (negative pregnancy test/end of pregnancy, if successful cycle), respectively.

At baseline, clinical information and index- pregnancy/ART cycle details are obtained from all women by a specially trained staff (Table 2). Data are collected by means of questionnaires and recorded in a web-based database including an electronic form for each woman enrolled. To ensure high quality data, a centralized data management performs quality control and plausibility checks according to predefined procedures. Follow-up data (Table 2) are collected during the three trimesters of pregnancy and in the puerperium period (6 weeks after delivery), at the time of hospital stay, routine clinical follow-up visits or telephone interviews.

**Table 2 Tab2:** Baseline and Follow-up data for evaluation and monitoring of women enrolled in the OTTILIA and FIRST registries

OTTILIA	
Baseline Clinical information: • Maternal age • Body Mass Index • Smoking habit • Reproductive history (previous pregnancies and obstetric complications occurred) • Personal and family history of VTE • Presence of inherited or acquired thrombophilias • Thrombophilic risk factors Index-pregnancy information: • Results of performed imaging tests, (ultrasonography, Doppler ultrasonography) • Invasive prenatal testing (i.e. villous sampling, amniocentesis) • Antithrombotic prophylaxis (brand, doses/day, duration)	Follow-up Pregnancy outcomes: • Live birth (gestational age, delivery mode, sex, birth weight, fetal or maternal hemorrhage) • Obstetric complications (PL, IUFD, gestational hypertension, preeclampsia, HELLP syndrome, SGA newborns, placental abruption) • VTE
FIRST	

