### Study size estimation

In the literature, the likelihood of observing live births without any treatment is estimated to range between 55 and 80% [2]; a multicentre Italian study [9] showed the occurrence of complications in 50% of all untreated women during pregnancy. Given these estimates, for the OTTILIA register, in order to observe an absolute increase of 15–20% (statistical power: 80%, significance level: 0.05), we calculated the inclusion of 190–340 thrombophilic women and, simultaneously, a cohort of pregnant women with the same clinical history (see inclusion criteria) not carrying inherited thrombophilia, in a ratio of at least 1:1. Thus, an overall number of 380–680 consecutive pregnancies are needed.

As far as the FIRST register is concerned, we estimated the inclusion of 624 women. This estimate is calculated on the basis of (1) the probability of observing live births after ART procedures (20–30%), (2) the estimate of an absolute increase of 5–10% in the number of live births after a prophylaxis of LMWHs (statistical power: 80%, significance level: 0.05).

It has been estimated that the OTTILIA and FIRST registries will be executed in the periods February 2012–December 2020 and October 2015–September 2020, respectively. In both the registries, an additional period of 9 months from the date of the last enrollment will be considered.

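### OTTILIA codes women never tested for thrombophilia as non-carriers, so the comparison cohort can contain unrecognised carriers and the carrier contrast can be biased

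*Protocol article*

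**What the plan says.** All references are to the protocol article.

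- **Participants**, on who is tested in OTTILIA: "Women eligible for the OTTILIA register can undergo thrombophilia test before conception, according to local policy".
- **Participants**, on those who are not: "If the test is not available or the test was not prescribed by the physician, women included are considered as non- carriers".
- **Study size estimation**, first cohort: "we calculated the inclusion of 190–340 thrombophilic women". Second cohort: "a cohort of pregnant women with the same clinical history (see inclusion criteria) not carrying inherited thrombophilia, in a ratio of at least 1:1". Together: "an overall number of 380–680 consecutive pregnancies are needed".
- **Study procedure, Table 2**, the OTTILIA baseline item: "Presence of inherited or acquired thrombophilias". The table lists no item for whether a test was done.
- **Aims**: primary aim 1 concerns factors associated with reproductive outcome. Primary aim 3 concerns the characteristics of women who may benefit from antithrombotic treatment.
- **Background**: thrombophilia, inherited or acquired, is presented as a possible cause of reproductive failure.
- **Statistical analysis plan**: missing data are to be prevented and queried. Sensitivity analysis of sub-groups, propensity-based stratification and logistic regression are planned. Women who were never tested are not mentioned.

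For FIRST, the Participants section uses thrombophilia status only where it is known and does not recode the rest.

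**The concern.** Carrier status defines the two OTTILIA cohorts and is an obvious candidate both as a risk factor (aim 1) and as an effect modifier (aim 3). The rule gives a definite negative value to women whose status nobody knows.

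Two features make this more than a coding convenience. First, being untested is not a random event: it follows local policy and physician choice, in a registry open to both obstetric departments and thrombosis centres. The non-carrier label is therefore partly a marker of where and by whom a woman was seen. Second, the planned safeguards do not reach it. A woman already defined as a non-carrier no longer has a missing value to query, and neither propensity stratification nor regression repairs a covariate that has been miscoded.

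At stake are the estimated association of thrombophilia with live birth and any statement about whether LMWH works differently in carriers and non-carriers.

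**Working it through.** **1. What the stated size rests on.** Inputs from Study size estimation: an increase of 15–20 points, power 80%, significance level 0.05, and a 50% complication rate in untreated women. Sidedness is not stated; two-sided is taken. The usual formula for two proportions (pooled variance under the null, equal groups, no continuity correction) is

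n per group = [1.96·√(2p̄(1−p̄)) + 0.842·√(p₁(1−p₁)+p₂(1−p₂))]² / (p₂−p₁)².

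- 50% v 65%: 170 per group, 340 in total.
- 50% v 70%: 93 per group, 186 in total, close to 190.

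The stated 190–340 is thus reproduced as the total of two equal groups within the thrombophilic cohort. Doubling it for the non-carrier cohort gives 380–680. A 55% baseline gives totals of 326 and 178 and fits less well. Read instead as a carrier versus non-carrier comparison at 80% power, the same inputs would need 170 and 93 women per cohort, not 340 and 190. The 15–20 points therefore look like a treatment effect among thrombophilic women. This is a reconstruction; the article does not spell it out.

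**2. Which comparisons the rule touches.** Misclassification runs one way: carriers can be labelled non-carriers, but not the reverse. The known-carrier group stays clean, and so does treated v untreated within it. Comparisons that use the labelled non-carriers are exposed.

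**3. Dilution of the carrier contrast.** Let D be the true difference in live birth (non-carriers minus carriers) and f the share of labelled non-carriers who are carriers. If misclassification is unrelated to outcome, observed difference = (1 − f)·D.

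The documents give neither the untested share nor the carrier share among the untested. Assume 30–70% and 10–30%, for illustration only:

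- low: f = 0.3 × 0.1 = 0.03; 15 × 0.97 = 14.6 points
- high: f = 0.7 × 0.3 = 0.21; 15 × 0.79 = 11.9 points

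For scale, with assumed live birth of 70% in non-carriers and 55% in carriers and 190 women per cohort, power is 86% at f = 0, 78% at f = 10% and 67% at f = 20%. With 340 per cohort it is still 90% at f = 20%.

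**4. When testing is related to outcome.** Let u be the untested share of labelled non-carriers and δ the difference in live birth between untested and tested women that is not due to carrier status (history, centre). Then observed difference = (1 − f)·D + u·δ. The dilution f·D is exactly offset when δ = f·D/u:

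- low: 0.03 × 15 / 0.3 = 1.5 points
- high: 0.21 × 15 / 0.7 = 4.5 points

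A larger positive δ makes the observed contrast too big; a negative δ makes it smaller still. The direction is not known in advance.

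**5. The who-benefits analysis.** Suppose LMWH adds 15–20 points in carriers and nothing in true non-carriers, and f = 20% in both treated and untreated labelled non-carriers. The apparent benefit in labelled non-carriers is 0.20 × 15 to 0.20 × 20 = 3–4 points, and the interaction shrinks from 15–20 to 12–16 points. If f differs by treatment and LMWH has no effect at all, the apparent effect is (f untreated − f treated)·D. With 21% and 3% this is 0.18 × 15 = 2.7 points in favour of LMWH; with the shares reversed it is 2.7 points against.

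**6. Cohort wording.** The first cohort is thrombophilic women without qualification. The second is women "not carrying inherited thrombophilia, in a ratio of at least 1:1". Background counts antiphospholipid-antibody syndrome as an acquired thrombophilia, and Table 2 records both kinds. A woman with acquired thrombophilia only fits both descriptions.

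**The case against.** The strongest reply is that the comparison the registry appears to be sized for is untouched: known carriers are correctly labelled, so treated v untreated within them is sound. That stands. A reader might infer that the rule makes the stated size too small, for example by 1/(1 − f)², or 1.06 to 1.60 times for f of 3–21%. The documents do not support this, since no carrier versus non-carrier difference is specified or sized.

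It can also be said that the amount of contamination is unknown and, at the low end, trivial (14.6 points instead of 15). That stands too; every value of f above is an assumption.

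A reader might further infer that unrecognised carriers must gather among untreated women, because nobody could prescribe for a status nobody knew. The documents say only that treatment follows current practice. All OTTILIA women have recurrent loss or fetal death, so LMWH may be given on history alone. Concentration is possible, not shown.

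Finally, restricting the main contrast to tested women has its own price: it selects on a decision that depends on centre and history, in a registry meant to represent consecutive women. This is a real cost and has to be reported, but it does not argue for treating untested women as tested negative.

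**Conclusion.** The concern holds for OTTILIA as a matter of the rule as written. Coding unknown as negative lets unrecognised carriers into the comparison cohort, and nothing in the planned analysis corrects it.

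The size cannot be determined from the documents. Under misclassification unrelated to outcome, a 15-point carrier difference would appear as 14.6–11.9 points for an assumed f of 3–21%. If testing tracks history or centre, the net bias may go either way, and treatment comparisons among labelled non-carriers may also be affected. It would be wrong to assume that the error only pulls estimates toward zero.

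The point does not reach the treated v untreated comparison in known carriers, the 380–680 total, or FIRST. The overlap for acquired-only thrombophilia is a separate, secondary defect of definition that the figures above do not cover.

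**What to change.** - Replace the rule with three levels: tested positive, tested negative, not tested. The article does not show that test status is on file; Table 2 names only presence of thrombophilia. Where the form holds nothing more, recover test status through the query system already planned.
- Make tested positive v tested negative the main carrier contrast and the basis of the LMWH-by-thrombophilia analysis, adjusted for centre and obstetric history.
- Keep untested women as a separate level in the other models, and show the present coding as a sensitivity analysis.
- Assign women with acquired thrombophilia only to one stated stratum, and word the two cohorts so that they do not overlap.
- Compare baseline characteristics of tested and untested women, so that selection from the restriction is visible.

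Cost: changed wording and coding, some data queries in a registry with a start date of February 2012, fewer women in the comparison cohort, and possible selection from restricting to tested women. No woman's care changes.

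### OTTILIA classes untested women as thrombophilia non-carriers, so its comparison cohort mixes tested-negative women with women of unknown status; carrier v non-carrier contrasts are diluted and open to selection bias

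*Protocol article*

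**What the plan says.** Under Participants, the protocol article says that women eligible for OTTILIA "can undergo thrombophilia test before conception, according to local policy". The next sentence fixes how the others are handled: "If the test is not available or the test was not prescribed by the physician, women included are considered as non- carriers". For FIRST, the same paragraph does not require thrombophilia status and adds: "However, when information is available, it will be considered in final analysis".

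Study size estimation then builds OTTILIA from two cohorts. For the first, "we calculated the inclusion of 190–340 thrombophilic women". The second is "a cohort of pregnant women with the same clinical history (see inclusion criteria) not carrying inherited thrombophilia", in a ratio of at least 1:1, which gives 380–680 pregnancies in all.

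Table 2 lists the presence of thrombophilia at baseline, and no item on whether a test was done. The Statistical analysis plan section offers sub-group sensitivity analyses, queries for missing variables, logistic regression, and stratification on the propensity to be treated. None of these separates tested-negative from untested women or deals with who was tested.

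**The concern.** The rule turns an unknown exposure into a negative one. It is a stated classification, not a detail that a condensed article leaves to a fuller plan. It also sits badly with the description of the comparison cohort, because freedom from inherited thrombophilia has not been established for an untested woman.

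Two separate errors follow.

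- **Contamination.** Some untested women will be carriers. On its own, this pulls the carrier v non-carrier difference towards zero.
- **Selection.** Testing depends on centre policy and physician choice. A centre that never tests contributes only non-carriers, so carrier status becomes partly a marker of centre practice, and possibly of history and LMWH use. This can move the contrast in either direction.

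At stake are thrombophilia as a factor associated with outcome (within the first primary aim) and the LMWH effect by carrier status (a natural question under the third).

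**Working it through.** **Inputs from the protocol (Study size estimation).** 190–340 thrombophilic women; comparison cohort at least 1:1; absolute increase of 15–20 points; power 80%; significance level 0.05; complications in 50% of untreated women; live birth without treatment 55–80%.

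**Inputs assumed.** The protocol gives neither the share of the comparison cohort that is untested (w) nor the share of untested women who are carriers (q). I take w = 50–80% and q = 10–30%. The undetected-carrier share is f = w × q, which runs from 0.5 × 0.1 = 5% to 0.8 × 0.3 = 24%.

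**Step 1: the plan's own figure.** For two proportions, two-sided 0.05 (sidedness is not stated), pooled variance under the null:

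n per group = [1.96·√(2·p̄(1−p̄)) + 0.842·√(p1(1−p1) + p2(1−p2))]² / (p1−p2)²

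- 50% v 65%: n = 170 per group, total 340.
- 50% v 70%: n = 93 per group, total 186, close to the stated 190.

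So 190–340 reproduces as the total of a two-group comparison. The protocol does not name that comparison, and the non-carrier rule does not change the figure.

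**Step 2: contamination.** The observed non-carrier rate is (1−f)·p(non-carrier) + f·p(carrier), so the observed difference is (1−f) times the true one.

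- f = 5%: 15 × 0.95 = 14.25, or 14.3 points.
- f = 24%: 15 × 0.76 = 11.4 points.

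Power is Φ[(d − 1.96·SE0)/SE1], where d is the observed difference and SE0 and SE1 are the standard errors under the null and the alternative. For f = 10% and 190 per group, the rates are 50% v 63.5%, d = 0.135, SE0 = 0.0508, SE1 = 0.0504 and the power is Φ(0.70) = 76%. With true rates of 50% v 65%:

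| f | Observed difference (points) | Power, 190 per group | Power, 340 per group |
|---|---|---|---|
| 0 | 15.0 | 84% | 98% |
| 5% | 14.3 | 80% | 97% |
| 10% | 13.5 | 76% | 95% |
| 20% | 12.0 | 66% | 89% |

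**Step 3: selection.** Suppose carrier status has no effect, half the comparison cohort is untested, and the live birth rate of untested women differs by an assumed 10 points in either direction. The spurious difference is 0.5 × 10 = 5 points. For baseline live birth rates of 55% to 70%, the unadjusted chance of p < 0.05 is:

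- 190 per group: about 16–19%, against a nominal 5%;
- 340 per group: about 26–31%.

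If only a quarter is untested and the shift is 5 points, the chance is about 6%.

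**The case against.** The strongest reply is that the harm is bounded and partly handled. Dilution is modest under the assumed inputs. Reproductive history is collected, and confounder identification followed by logistic regression is planned, so selection through recorded history can be adjusted for. That stands for measured history. It does not reveal the status of untested women or deal with selection through factors not recorded.

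Four stronger readings are tempting, and the documents do not support them.

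- **A large false-positive rate.** Suppose all tested women had 3 losses (65% live birth) and all untested women had 2 (80%). With half the comparison cohort untested, the contrast is 65% v 72.5%, and p < 0.05 occurs in about 56% of registries (340 per group) or 35% (190 per group). This needs complete separation by number of losses and no adjustment. With an 80/20 split each way, carriers show 68%, non-carriers 72.5%, the gap is 4.5 points, and the figures are about 25% and 16%. OTTILIA also admits women with 2 losses only if at least one fetal karyotype was normal, so it is conjecture that they are the untested ones.
- **Every OTTILIA result is affected.** Women classed as carriers are not contaminated by the rule. An LMWH comparison within them is unaffected by this misclassification, and the sample size may rest on that comparison.
- **Testing status is lost.** The protocol says how untested women are regarded. It does not say that the database discards the information.
- **FIRST contradicts OTTILIA.** FIRST is a separate registry that does not require status, and the text does not say how its untested women are classed.

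**Conclusion.** The concern holds for carrier v non-carrier contrasts and for the LMWH effect by carrier status. Applied as written, the rule puts women of unknown status into a cohort described as non-carriers, and no stated analysis separates them.

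The dilution and power figures rest on assumed values of f and on true rates of 50% v 65%. That undetected carriers are present is an inference, though close to certain if an appreciable number of women are untested. The selection bias cannot be sized from the documents: the 5-point example rests on half the cohort being untested and a 10-point shift, before adjustment, and adjustment for reproductive history may reduce it. With the effect limited to these analyses and a remedy at hand, this is a should-fix point.

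**What to change.** Replace the rule by a three-level status: tested positive, tested negative, not tested. Base the main carrier v non-carrier contrast and the 1:1 comparison cohort on tested women, adjusted for reproductive history and centre. Report untested women as a separate group, and give the version with all women as a sensitivity analysis.

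The cost is a recode, plus queries to centres wherever testing was not recorded; the stated OTTILIA period starts in February 2012, so some of these would concern old records. The comparison cohort becomes smaller and its intervals wider. Tested women are themselves selected by centre and physician, so the contrast would apply to tested women only, and the report should say so.
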